## Special notes on response assessment

When nodal disease is included in the sum of target lesions and the nodes decrease to 'normal' size (<10 mm), they may still have a measurement reported on scans. This measurement should be recorded even though the nodes are normal in order not to overstate progression should it be based on increase in size of the nodes. As noted earlier, this means that patients with CR (complete response) may not have a total sum of 'zero' on the case report form (CRF).

In trials where confirmation of response is required, repeated 'NE' time point assessments may complicate best response determination. The analysis plan for the trial must address how missing data/assessments will be addressed in determination of response and progression. For example, in most trials it is reasonable to consider a patient with time point responses of PR-NE-PR as a confirmed response.

Patients with a global deterioration of health status requiring discontinuation of treatment without objective evidence of disease progression at that time should be reported as 'symptomatic deterioration'. Every effort should be made to document objective progression even after discontinuation of treatment. Symptomatic deterioration is *not* a descriptor of an objective response: it is a reason for stopping study therapy. The objective response status of such patients is to be determined by evaluation of target and non-target disease as shown in Tables belows.

# APPENDIX 6: PREGNANCY NOTIFICATION FORM

[figure not shown]

## Pregnancy Notification Form

TO BE FAXED TO VIGILANCE UNIT-N° [name]

|                            |                                          |                                                                                   |
|----------------------------|------------------------------------------|-----------------------------------------------------------------------------------|
| PROTOCOL: REGOMUNE  | EUDRACT/ID-RCB N°: 2016-005175-27 | COUNTRY: France                                                            |
| SPONSOR IDENTIFICATION N°: | INVESTIGATOR SITE :                      | SITE N°:                                                                          |
| DATE OF THIS REPORT:       | INITIAL REPORT   | FOLLOW-UP REPORT N°:                    
FINAL REPORT  |

THIS NOTIFICATION CONCERNS: ☐ PREGNANCY ☐ FEEDING

### 1. PATIENT IDENTIFICATION

INCLUSION N°: | | | | | AGE (AT TIME OF DISCOVERY): | | | | YEARS GENDER: FEMALE ☐ MALE ☐  
TREATMENT ARM: | | | DOSE LEVEL (ONLY FOR PHASE I STUDIES): | | | WEIGHT (Kg): | | | | HEIGHT (CM): | | | | BODY SURFACE AREA (M²): | | | |

### 2. INFORMATION ON PREGNANT

THE PREGNANT IS: THE PATIENT ☐  
A PATIENT PARTNER ☐ \*SPECIFY AGE (AT TIME OF DISCOVERY): | | | | WEIGHT (Kg): | | | | HEIGHT (CM): | | | | BODY SURFACE: | | | |  
DATE OF LAST MENSTRUAL PERIOD (DD/MM/YYYY): | | | | | ESTIMATED DATE OF DELIVERY (DD/MM/YYYY): | | | | |  
WAS THE PATIENT USING CONTRACEPTION? YES ☐ SPECIFY: ..... NO ☐ UNCERTAIN ☐  
DO YOU THINK THERE WAS A FAILURE IN CONTRACEPTION? YES ☐ NO ☐ UNKNOWN ☐  
CAUSE/REASON FOR FAILURE (NON-COMPLIANCE, MECHANICAL, DRUG INTERACTION...): .....  
MATERNAL PREGNANCY ASSOCIATED EVENTS (if yes, specify): .....  
IF THE MOTHER EXPERIENCED A SERIOUS ADVERSE EVENT DURING PREGNANCY, PLEASE COMPLETE A SAE FORM.

### 3. DRUGS INFORMATION

DESCRIBE ALL RELEVANT TREATMENTS ADMINISTERED TO THE PREGNANT AND HER PARTNER IF APPLICABLE (Date and dose of investigational drugs and concomitant treatments):

CONCERNING PATIENT INCLUDED IN THE STUDY:

| INVESTIGATIONAL PROCEDURE(S)
INDICATE THE INTERNATIONAL COMMON
DENOMINATION OF THE IMP* & OTHER
COMBINED AND/OR RADIOTHERAPY
AND/OR DEVICE AND/OR METHOD OR
ACTION | ROUTE | EVENT CYCLE
NUMBER | DATES                                                                              |                                                                                   | DOSES AND UNIT                                                |  |                                                                              |  |
|-----------------------------------------------------------------------------------------------------------------------------------------------------------------------------------|-------|-----------------------|------------------------------------------------------------------------------------|-----------------------------------------------------------------------------------|---------------------------------------------------------------|--|------------------------------------------------------------------------------|--|
|                                                                                                                                                                                   |       |                       | DATE OF FIRST ADMINISTRATION/USE
(1 st DAY OF 1 st CYCLE) | DATE OF LAST ADMINISTRATION/USE
(1 st DAY OF 1 st CYCLE) | LAST DAILY DOSE
ADMINISTERED BEFORE
PREGNANCY DISCOVERY |  | CUMULATIVE DOSE SINCE
THE 1 st ADMINISTRATION IF
APPLICABLE |  |
| 1.                                                                                                                                                                                |       |                       |                                                                                    |                                                                                   |                                                               |  |                                                                              |  |
| 2.                                                                                                                                                                                |       |                       |                                                                                    |                                                                                   |                                                               |  |                                                                              |  |
| 3.                                                                                                                                                                                |       |                       |                                                                                    |                                                                                   |                                                               |  |                                                                              |  |
| 4.                                                                                                                                                                                |       |                       |                                                                                    |                                                                                   |                                                               |  |                                                                              |  |
| 5.                                                                                                                                                                                |       |                       |                                                                                    |                                                                                   |                                                               |  |                                                                              |  |

\*IMP: INVESTIGATIONAL MEDICAL PRODUCT

DOES TREATMENT(S) STOPPED WHEN PREGNANCY WAS DISCOVERED: YES ☐ NO ☐

IF NO EXPLAIN AND GIVE THE STOP DATE FOR EACH TREATMENT OR PROCEDURE : .....

CONCERNING THE PREGNANT:

| CONCOMITANT DRUGS (INN) | ROUTE | DAILY DOSE | START DATE | STOP DATE | CHECK BOX
IF ONGOING  | INDICATION |
|-------------------------|-------|------------|------------|-----------|--------------------------|------------|
| 1.                      |       |            |            |           |  |            |
| 2.                      |       |            |            |           |  |            |
| 3.                      |       |            |            |           |  |            |
| 4.                      |       |            |            |           |  |            |
| 5.                      |       |            |            |           |  |            |
| 6.                      |       |            |            |           |  |            |

### 4. PARENTS RELEVANT MEDICAL HISTORY:

MOTHER:

RISK FACTORS (TICK IF YES): ☐ SMOKING, ☐ ALCOHOL, ☐ DRUG ABUSE, ☐ INFECTION, ☐ MEDICATION, ☐ HYPERTENSION, ☐ ECLAMPSIA, ☐ OTHERS, Specify: .....

RELEVANT MEDICAL HISTORY (include information on familial disorders, known risk factors or conditions that may affect the outcome of the pregnancy): .....

# Pregnancy Notification Form

TO BE FAXED TO VIGILANCE UNIT-N° [name]

|                                  |  |                                         |                         |                                       |
|----------------------------------|--|-----------------------------------------|-------------------------|---------------------------------------|
| PROTOCOL : REGOMUNE              |  | EUDRACT/ID-RCB N°: 2016-005175-27       |                         | COUNTRY: France                       |
| SPONSOR IDENTIFICATION N°:       |  | INVESTIGATOR SITE :                     |                         | SITE N°:                              |
| DATE OF THIS REPORT: [ ]/[ ]/[ ] |  | INITIAL REPORT  | FOLLOW-UP REPORT N° [ ] | FINAL REPORT  |
| INCLUSION N°: [ ]                |  | Age (YEARS OLD) : [ ]/[ ]/[ ]           |                         |                                       |

## MOTHER:

PREVIOUS OBSTETRIC HISTORY (PROVIDE ALL PREVIOUS PREGNANCIES INCLUDING ABORTION AND STILLBIRTH)

| DATE        | GESTATION WEEK | OUTCOME |
|-------------|----------------|---------|
| [ ]/[ ]/[ ] |                |         |
| [ ]/[ ]/[ ] |                |         |
| [ ]/[ ]/[ ] |                |         |
| [ ]/[ ]/[ ] |                |         |

## FATHER:

RELEVANT MEDICAL HISTORY:

## 5. PREGNANCY OUTCOME

☐ NOT APPLICABLE AT THE TIME OF DECLARATION ☐ APPLICABLE (COMPLETE BELOW)

|                                                                 |                                                                                                                                                                                                                                       |                                                                                    |
|-----------------------------------------------------------------|---------------------------------------------------------------------------------------------------------------------------------------------------------------------------------------------------------------------------------------|------------------------------------------------------------------------------------|
|  DELIVERY
[ ]/[ ]/[ ]
(DOMM/YYYY) |  NORMAL
 FORCEPS/VENTOUSE
 CESAREAN
 PLANNED
 THERAPEUTIC
 SPONTANEOUS | MATERIAL COMPLICATIONS OR PROBLEMS RELATED TO BIRTH

SPECIFY REASONS

 |
|  ABORTION
[ ]/[ ]/[ ]
(DOMM/YYYY) |                                                                                                                                                                                                                                       |                                                                                    |

OTHER INFORMATION (for example in case of not yet delivery provide results of specific tests performed e.g. amniocentesis, ultrasound, maternal serum afp, serology tests etc):

ASSESSMENT OF CAUSALITY: PLEASE INDICATE THE RELATIONSHIP BETWEEN THE PREGNANCY OUTCOME AND IMP:

☐ Not Related ☐ Related, specify IMP: \_\_\_\_\_

## 6. CHILD INFORMATION (if applicable)

NEONATE:

☐ NORMAL ☐ STILLBIRTH ☐ ABNORMAL, SPECIFY: \_\_\_\_\_

OTHERS INFORMATION:

SEX: MALE ☐ FEMALE ☐ HEIGHT: \_\_\_\_\_ CM WEIGHT: \_\_\_\_\_ KG OTHER: \_\_\_\_\_

## 7. INFORMATION ON FEEDING

☐ NOT APPLICABLE

DATE OF FIRST FEEDING (DD/MM/AAAA): [ ]/[ ]/[ ]

☐ APPLICABLE (COMPLETE BELOW)

DATE OF LAST FEEDING (DD/MM/AAAA): [ ]/[ ]/[ ]

DESCRIBE ALL RELEVANT INFORMATION: \_\_\_\_\_

## 8. FOLLOW-UP INFORMATION

FOLLOW-UP INFORMATION CAN BE OBTAINED FROM:

DOCTOR: \_\_\_\_\_ INSTITUTION: \_\_\_\_\_ ADDRESS: \_\_\_\_\_

E-MAIL: \_\_\_\_\_ PHONE: \_\_\_\_\_ FAX: \_\_\_\_\_

## 9. INVESTIGATOR

NAME: \_\_\_\_\_ INSTITUTION: \_\_\_\_\_

E-MAIL: \_\_\_\_\_

PHONE: \_\_\_\_\_

FAX: \_\_\_\_\_

DATE (DDMMYYYY): [ ]/[ ]/[ ]

SIGNATURE: \_\_\_\_\_

## APPENDIX 7: DOSE MODIFICATION/DELAY FOR TOXICITIES RELATED TO REGORAFENIB (EXCEPT FOR HAND-FOOT SYNDROME REACTION, HYPERTENSION, AND ALT AND/OR AST AND/OR BILIRUBIN INCREASES)

| NCI-CTCAE v5.0 | Dose interruption                       | Dose modification c                                                                             | Dose for subsequent cycles      |
|----------------|-----------------------------------------|------------------------------------------------------------------------------------------------------------|---------------------------------|
| Grade 0-2      | Treat on time                           | No change                                                                                                  | No change                       |
| Grade 3        | Delay until $\leq$ grade 2 a | Reduce 1 dose level                                                                                        | No possibility of re-escalation |
| Grade 4        | Delay until $\leq$ grade 2 b | Reduce 1 dose level
Permanent discontinuation must be discussed with the sponsor in case of recurrence. |                                 |

a- Excludes alopecia, non-refractory nausea/vomiting, non-refractory hypersensitivity and asymptomatic laboratory abnormalities

b- If no recovery after a 4 weeks delay, treatment will be permanently discontinued.

c For cohort [A], regorafenib should be interrupted and no dose reduction are allowed. Patients requiring a delay of > 4 weeks should permanently discontinue regorafenib.

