| AST or ALT > 5 x ULN to ≤20 x ULN and/or total bilirubin > 3 x ULN to ≤ 10 x ULN            | 1st occurrence :
Interrupt Regorafenib treatment.
Monitor transaminases weekly until return to <3 times ULN or baseline.
Restart: If the potential benefit outweighs the risk of hepatotoxicity, decrease dose by one dose level, and monitor liver function weekly for at least 4 weeks.

Re-occurrence : Discontinue permanently | discontinue Avelumab therapy

Increase frequency of monitoring to every 1 to 2 days
1 to 2 mg/kg/day prednisolone or equivalent

Add prophylactic antibiotics for opportunistic infections
Consult gastroenterologist / hepatologist
Consider obtaining MRI/CT scan of liver and liver biopsy if clinically warranted

If returns to <3 times ULN or baseline:
Taper steroids over at least 1 month
If does not improve in > 3 to 5 days, worsens or rebounds: |
| >20 times ULN
or >3 times ULN with concurrent bilirubin > 2 times ULN                    | Any occurrence
Discontinue permanently
Monitor liver function weekly until resolution or return to baseline.                                                                                                                                                                                                                                | Add mycophenolate mofetil 1 gram (g) twice daily
If no response within an additional 3 to 5 days , consider other immunosuppressants per local guidelines
Re-occurrence : Discontinue permanently                                                                                                                                                                                                                                                                                         |

a For cohort [A], regorafenib should be interrupted and no dose reduction are allowed. Patients requiring a delay of > 4 weeks should permanently discontinue regorafenib

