| Grade 2
Diarrhea: 4 to 6 stools per day over baseline; IV fluids < 24h; not interfering with ADL
Colitis: abdominal pain; blood in stool                                                                                                                    | No change                                                                                                                                                       | Withhold Avelumab therapy
Symptomatic treatment                                                                                                                                                                          | If improves ≤ grade 1: Resume Avelumab therapy
If persists >5-7 days or recurs, treat as grade 3 or 4                                                                                                                                                                                                                                             |
| Grade 3 to 4
Diarrhea (Grade 3): ≥ 7 stools per day over Baseline; incontinence; IV fluids ≥ 24h; interfering with ADL
Colitis (grade 3): severe abdominal pain, medical intervention indicated, peritoneal signs
Grade 4: life-threatening, perforation | Delay until ≤ grade 2 and reduce 1 dose level for grade 3

Permanently discontinue for grade 4, recurrent grade 3 or in case of no recovery after 4 weeks | Withhold for grade 3

Permanently discontinue for grade 4 or recurrent grade 3
1.0 to 2.0 mg/kg/day prednisone or equivalent add prophylactic antibiotics for opportunistic infections
Consider lower endoscopy | If improves:
Continue steroids until grade ≤1, then taper over at least 1 month; resume Avelumab therapy following steroids taper (for initial Grade 3).

If worsens persists > 3 to 5 days, or recur after improvement:
Add infliximab 5mg/kg (if no contraindication),
Note: infliximab should not be used if perforation or sepsis |

a For cohort [A'], regorafenib should be interrupted and no dose reduction are allowed. Patients requiring a delay of > 4 weeks should permanently discontinue regorafenib

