| Grade 4
Creatinine increased > 6 x ULN                | Permanently discontinue for grade 4                                                | Permanently discontinue Avelumab therapy
Monitor creatinine daily
1.0 to 2.0 mg/kg/day prednisone or equivalent.
Add prophylactic antibiotics for opportunistic infections
Consider renal biopsy
Nephrology consult | If returns to Grade ≤1:
Taper steroids over at least 1 month.                                                                                           |

a For cohort [A'], regorafenib should be interrupted and no dose reduction are allowed. Patients requiring a delay of > 4 weeks should permanently discontinue regorafenib

| Myocarditis                                                                                                                                                                                                                                                                                                                                                                                                                                                                                      | Initial Management                                                                                                                                                                                                                                                                                                                                                                                                                                           | Follow-up Management                                                                                                                                                                                                                                                                                                             |

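### For the same event, the regorafenib rules in Appendices 7 and 8 call both for resuming at a lower dose and for stopping permanently

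*Protocol*

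**What the plan says.** Appendix 7 is a table by CTCAE grade for toxicities related to regorafenib. Its title removes three groups from its scope: "EXCEPT FOR HAND-FOOT SYNDROME REACTION, HYPERTENSION, AND ALT AND/OR AST AND/OR BILIRUBIN INCREASES". Diarrhoea, rash and creatinine increase therefore stay inside it. For both Grade 3 and Grade 4 it asks for a delay until Grade 2 or better and then "Reduce 1 dose level". In the Grade 4 row it adds "Permanent discontinuation must be discussed with the sponsor in case of recurrence", and a footnote to that row says "If no recovery after a 4 weeks delay, treatment will be permanently discontinued". The Grade 3 row has no stop on recurrence.

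Appendix 8 is organised by event and has a regorafenib column. For Grade 3 to 4 diarrhoea/colitis, and again for Grade 3 to 4 rash, that column reads "Permanently discontinue for grade 4, recurrent grade 3 or in case of no recovery after 4 weeks". For Grade 4 creatinine it reads "Permanently discontinue for grade 4".

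In the Appendix 8 liver table, the third row is defined by "AST or ALT > 5 x ULN to ≤20 x ULN and/or total bilirubin > 3 x ULN to ≤ 10 x ULN". At first occurrence it has regorafenib interrupted, with a possible restart one level lower. The last row covers values above 20 times ULN "or >3 times ULN with concurrent bilirubin > 2 times ULN", and at any occurrence it requires permanent discontinuation.

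Section 7.6.2 sends sites to both appendices together. It gives a tie-break for a patient who has several adverse events with conflicting recommendations: take the one leading to the lowest dose level.

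**The concern.** Two investigators who both follow the protocol can act in opposite ways on the same event: one restarts regorafenib at a lower level, the other never gives it again. The events concerned are Grade 4 toxicities, recurrent Grade 3 diarrhoea or rash, and a combined rise in transaminases and bilirubin. For patients with normal baseline values, Section 11.4 treats ALT or AST above 3 times ULN with bilirubin above 2 times ULN as potential drug-induced liver injury, and it points to Appendix 8 for management.

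What is at stake is patient safety and the ability to check adherence. Section 5.3 classes incorrect dosing through failure to follow the dose-adjustment rules as a deviation that might affect patient safety. Where two written rules disagree, a monitor cannot say which action was the deviation.

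**Working it through.** No sample size, power or error rate is involved, so the check sets the rules side by side and intersects the liver ranges.

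**Appendix 7 against Appendix 8, regorafenib action**

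| Event | Appendix 7 | Appendix 8 | Agree? |
|---|---|---|---|
| First Grade 3 diarrhoea or rash | Delay to ≤ Grade 2, one level lower | Delay to ≤ Grade 2, one level lower | Yes |
| First recurrence of Grade 3 diarrhoea or rash | Delay to ≤ Grade 2, one level lower again | Permanent stop | No |
| First Grade 4 diarrhoea or rash | Delay to ≤ Grade 2, one level lower; stop only if no recovery after 4 weeks | Permanent stop | No |
| First Grade 4 creatinine | Same as the row above | Permanent stop | No |

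The Appendix 7 footnote that sets aside asymptomatic laboratory abnormalities is attached to the Grade 3 row only. It does not take Grade 4 creatinine out of the table.

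**When Section 7.6.2 would stop a repeated Grade 3 event.** Section 7.3 gives the phase II dose outside cohort A' as 160 mg. At that dose, Section 7.6.2 requires a permanent stop once more than 2 reductions are needed, or when a delay exceeds 4 weeks. The levels are 160, 120 and 80 mg. If each Grade 3 event resolves within 4 weeks and no other event has used up a reduction:

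- First Grade 3: 160 to 120 mg (reduction 1)
- First recurrence: 120 to 80 mg (reduction 2, still allowed)
- Second recurrence: a third reduction would be needed, 3 > 2, so stop

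Appendix 8 stops at the first recurrence. The two routes therefore differ by one recurrence.

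**Liver table, within Appendix 8 only.** Because the third row joins its two ranges with and/or, one value in range is enough.

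- Third row (T): ALT/AST in (5, 20] x ULN, or bilirubin in (3, 10] x ULN
- Last row (L): ALT/AST > 20 x ULN, or ALT/AST > 3 x ULN together with bilirubin > 2 x ULN

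Both rows apply in two regions:

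1. ALT/AST in (5, 20] with bilirubin > 2. The ALT/AST value alone meets T. Since ALT/AST > 5 > 3 and bilirubin > 2, L is met.
2. Bilirubin in (3, 10] with ALT/AST > 3. The bilirubin value alone meets T. Since ALT/AST > 3 and bilirubin > 3 > 2, L is met.

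Example: ALT 10 x ULN and bilirubin 4 x ULN. 10 lies in (5, 20] and 4 lies in (3, 10], so T applies (interrupt, possible restart lower). 10 > 3 and 4 > 2, so L applies (permanent stop).

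The second liver row is left out of the argument, because its regorafenib cell is blank in the text available.

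**The case against.** The strongest reply is that the protocol is not silent when rules meet. Section 7.6.2 calls its rules guidelines and refers any severe toxicity to the principal investigator to decide management. It also has a tie-break, and it caps dose reductions and delays. A reader may also take the event-specific Appendix 8 to override the generic Appendix 7, and take the last liver row as a special case mirroring the thresholds in Section 11.4.

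Part of this stands. The referral softens the practical effect. The cap means that a reader who infers that repeated Grade 3 events never reach a mandatory stop outside Appendix 8 would be mistaken: the stop comes, but later.

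The rest does not settle the matter. A referral does not say which written rule applies. The tie-break addresses several adverse events and chooses a dose level; a Grade 4 diarrhoea is one event, and the choice is between restart and stop. For the liver table one could argue that a transaminase rise and a bilirubin rise are two events, but the last row treats the combination as a single criterion and the third row has no exception for it. Specific-over-general is a reasonable habit, but the protocol never states it. Appendix 7 lists its exclusions by name, and these three toxicities are not among them. Nor is Appendix 8 confined to immune-related cases: its title names toxicities of both drugs, and its regorafenib entries for diarrhoea, rash and creatinine carry no such limit.

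**Conclusion.** The rules are wrong as written. There are two separate contradictions. Appendix 7 and Appendix 8 disagree on a first Grade 4 diarrhoea/colitis, rash or creatinine increase, and on a first recurrence of Grade 3 diarrhoea/colitis or rash. Within Appendix 8, the third and last liver rows overlap with opposite actions. The conclusion rests on the literal scope of the Appendix 7 title and on the absence of a precedence clause. The comparison in dose levels applies to cohorts where reduction is allowed; cohort A' allows none.

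Four stronger readings are not supported:

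- A reader might infer that Appendix 7 keeps dosing through a Grade 3 or 4 event. It does not: it delays, then resumes at a reduced level.
- A reader might take the liver problem as a third clash between the appendices. Appendix 7 excludes liver tests, so that overlap lies inside Appendix 8.
- A reader might size the problem from the 41% diarrhoea and 18% maculopapular rash in Section 1.2.3. Those rates carry no grade restriction, so they say nothing about Grade 4 or recurrent Grade 3 events. The protocol gives no rate for the events in conflict, and how often they would arise cannot be derived from it.
- A reader might infer damage to the efficacy conclusions. No primary endpoint definition, decision boundary or sample size changes, each phase II trial is single-arm and analysed on its own, and discontinuation for toxicity is not a listed endpoint.

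**What to change.** The sponsor should:

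1. Reconcile Appendix 7 with the regorafenib columns of Appendix 8 for diarrhoea/colitis, rash and creatinine. Either exclude from Appendix 7 the toxicities that have their own column in Appendix 8, or make the entries identical.
2. Rewrite the liver rows so that each combination of ALT/AST and bilirubin falls in exactly one row.
3. State in Section 7.6.2 which appendix takes precedence when one event is covered by both.

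Which action applies in each case is for the sponsor to decide; none is proposed here. The cost is a protocol amendment to two appendix tables and one sentence in Section 7.6.2, with no extra patients or procedures.
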